#### Process Evaluation

Process Evaluation questionnaires will be used at baseline and month 6. Various approaches were selected and combined in the questionnaires to incorporate the components recommended by the Medical Research Council guidelines.^46^ Fidelity and quality of implementation of the intervention will be assessed using open-response questions, to get a general overview of acceptability, as previously demonstrated in the WATCH IT evaluation,^62^ and specific Likert-ranked questions, to examine participant perceptions of the strengths and weaknesses of the programme, as used in the SHED-IT evaluation.^63^ Assessment of diet intrusiveness, the participants’ intention to make changes and self-belief in success, will be used to support clarification of causal mechanisms. Contextual factors associated with variation in outcomes will be identified via a validated measure of self-efficacy for fat intake behaviour, containing three task-specific domains of self-efficacy (negative mood, positive mood and food availability), which have been shown to predict different types of fat reduction behaviours in low-income populations, with variations according to race.^64^ In trials, such as this one, where blinding is not possible, the patient's preference for treatment can influence the outcome, especially where the participant is not simply a passive recipient of the intervention, but is required to engage and make lifestyle changes. Therefore, intervention group preferences will be elicited before each randomisation, and used subsequently in the analysis of covariance (ANCOVA) to investigate the influence on LDL-cholesterol of participants’ preferences at baseline.^65^

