#### Interviews

Qualitative data will be collected from a sample of participants at the end of the 6-month intervention period. Participants will be purposively selected from the Diet2 arm to include men and women of different ethnicities, with high and low levels of adherence, to reflect the diversity and breadth of experiences of a wide range of participants. Semistructured interviews will be conducted using open-ended, non-directive questions. The aim will be to understand participants’ experience of implementing dietary changes by enabling them to ‘tell their story’—what they did and how—as well as identifying barriers to, and enablers of, success in making and maintaining diet changes. It is anticipated that there will be variations in the effectiveness of the dietary intervention for different individuals in different sociocultural settings. Analysis of the interview data will serve to describe and potentially explain these differences and the factors involved. By exploring participant views on the intervention, study design and delivery, the interviews will identify problems at the feasibility stage to prevent them occurring at the full trial stage.

Written informed consent for digital recording of the 30–60 min interview will be sought prior to booking a mutually agreed time and place, enabling the interview to be conducted either in participants’ homes or a clinic room with privacy. Participants will be encouraged to invite their partner, family member or other cohabitant to join in the interview and give their perspective on how dietary changes are lived.

The sample size will be around 10 although the actual number recruited will be determined at the point at which the researcher is satisfied that a good understanding of the barriers and facilitators to making dietary changes has been achieved.

Interviews will be transcribed verbatim. Data analysis will be conducted following the Framework Method: familiarisation, identifying a thematic framework, indexing, charting, mapping and interpretation.^68^

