### Outcome measures

The primary outcomes for this study are feasibility and acceptability of trial procedures for recruitment, retention, data completion and the intervention. The protocol will be considered viable for a definitive RCT without modification if the following outcomes are met:
Recruitment rates of at least 50% of eligible patients;Attrition rate of <20% by 6 months;Compliance rate of 60% to trial.

If these outcomes are not met, the protocol will be modified in light of the study's findings.

Recruitment rate will be measured as proportion of eligible patients who are subsequently enrolled. Methods of recruitment will be compared: difference between recruitment rate from systematic methods (screening results) and ad hoc methods (posters, referral by multidisciplinary team). Reasons will be sought for declined participation. Appropriateness of eligibility criteria and their practical application for definitive trial will be explored.

Attrition rate is defined as both discontinuation and loss to follow-up of participants at 6 months. Logistic regression will be conducted to assess whether completion is associated with age, gender or allocation preference. Reasons for discontinuation will be sought from participants. The target of 20% (with precision of 10%) is based on the mean attrition rate from five Portfolio Diet studies (13%) and systematic review evidence (18%),^20^ although attrition has ranged from 25%^24^ to 42%^73^ in other HIV diet studies. Acceptability of the intervention and group allocation will be explored by questionnaire, and assessed by comparing attrition rates between the two groups.

Attendance to appointments, collection of supplied foods and completion of food diaries will be used as indicators of participation and study compliance.

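### Participants who leave before month 6 have no scheduled point at which to rate acceptability, so the questionnaire and interview findings will mainly reflect those who stay

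*Protocol article*

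**What the plan says.** All places are in the Protocol article.

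- **Outcome measures** makes acceptability primary: "The primary outcomes for this study are feasibility and acceptability of trial procedures for recruitment, retention, data completion and the intervention".
- The same section says how it is judged: "Acceptability of the intervention and group allocation will be explored by questionnaire, and assessed by comparing attrition rates between the two groups".
- **Process Evaluation** fixes the questionnaire's timing: "Process Evaluation questionnaires will be used at baseline and month 6". Its content includes open questions on acceptability, Likert items on the programme's strengths and weaknesses, and an assessment of how intrusive the diet is.
- **Interviews** fixes the qualitative timing: "Qualitative data will be collected from a sample of participants at the end of the 6-month intervention period". The sampling is described as follows: "Participants will be purposively selected from the Diet2 arm to include men and women of different ethnicities, with high and low levels of adherence". About ten interviews are planned, and one stated use is to find problems before the full trial.
- **Outcome measures** also deals with leavers: "Attrition rate is defined as both discontinuation and loss to follow-up of participants at 6 months"; "Reasons for discontinuation will be sought from participants"; "Logistic regression will be conducted to assess whether completion is associated with age, gender or allocation preference". Attrition has its own progression limit of under 20% by 6 months.
- **Dissemination** adds that people who withdraw from the intervention are asked to allow data collection at routine clinic appointments.

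**The concern.** Leaving a dietary trial is often a sign that the diet, the allocation or the trial burden did not suit the person. The article accepts this link, since it uses attrition to assess acceptability. Yet both instruments that record the participant's own view of the diet after trying it are timed at or after the point where attrition is counted. As scheduled, they answer how acceptable the diet is to those who stayed, whereas the Study objectives ask about participants in general.

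At stake is the guidance the pilot gives on redesign. If the people for whom the diet failed are largely absent from the ratings and interview themes, the changes made for the definitive trial may address the difficulties of stayers and leave the causes of attrition untouched. The pilot's sample size was chosen to estimate attrition, so this is the group it most needs to understand.

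**Working it through.** **1. Who could be missing.** Inputs: 60 participants and 20% expected attrition (Sample size); 1:1 allocation (Allocation strategy).

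- The plan's own precision first: 0.20 ± 1.96 × √(0.20 × 0.80 / 60) = 0.20 ± 0.101, which is 9.9% to 30.1%. The stated 10% to 30% reproduces.
- Expected leavers by month 6: 0.20 × 60 = 12, or about 6 of 30 per arm.
- A result that meets the attrition criterion can still contain many leavers: 11/60 = 18.3%, which is under 20%.

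**2. What is scheduled for a participant who leaves before month 6.**

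| Source of information | When | Reaches an early leaver? |
|---|---|---|
| Process questionnaire | Baseline | Yes, but before any exposure to the diet |
| Process questionnaire | Month 6 | No time point set for leavers |
| Interviews (Diet2 only) | End of the 6 months | Not excluded, but discontinuation is not a sampling criterion |
| Attrition count, compared by arm | 6 months | Yes, as a count |
| Reasons for discontinuation | Time not stated | Yes, but not the structured items |
| Regression of completion | Analysis | Yes, on age, gender and allocation preference only |
| Routine clinic data after withdrawal | Routine visits | Yes, if agreed; the questionnaire is not mentioned |

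Sampling interviewees for low adherence does not replace sampling leavers. Under Dietary assessment, the functional-food compliance score is taken at months 6 and 12, so someone who left earlier would normally have no score by which to be chosen. Diet1 participants are not interviewed, although acceptability of group allocation is to be assessed.

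**3. How far the attrition comparison fills the gap.** With 30 per arm and 20% loss in each, the 95% half-width for the difference is 1.96 × √(2 × 0.20 × 0.80 / 30) = 0.202, about ±20 percentage points. Attrition is also a mixed signal: it pools discontinuation with loss to follow-up, and under Dissemination some participants are withdrawn because of a lipid result, which says nothing about whether they liked the diet.

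**4. Why the effect cannot be sized.** Suppose a share A of completers rated the diet acceptable, attrition was d, and no leaver answered. The share among all randomised would then lie between (1 − d)A and (1 − d)A + d. The article defines no such share, so A is purely an assumption. For A = 80%:

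- d = 10%: 72% to 82%
- d = 20%: 64% to 84%
- d = 30%: 56% to 86%

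At d = 20%, the range is 56% to 76% for A = 70% and 72% to 92% for A = 90%. Each range contains A, so arithmetic alone does not fix even the direction. A downward shift follows only if leavers are assumed to be less satisfied, which is plausible but not documented.

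**The case against.** The strongest reply is that the plan does not ignore leavers. Outcome measures never equates acceptability with the questionnaire result: leaving is itself used as evidence, reasons are sought, and completion is related to allocation preference. This stands. A reader might infer that leavers go unmeasured and that reported acceptability is therefore overstated by some number of points. The article does not support that. Leavers are counted and asked why, and the percentage to be overstated is not defined.

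A reader might also infer that high loss common to both arms would pass unnoticed, because only a between-arm comparison is planned. It would not: the overall limit of under 20% would be failed. Nor is 30% a tolerated rate; it is the upper confidence limit around an expected 20%.

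It can further be said that a time point is not an eligibility rule, that nothing bars a leaver from completing a form or an interview at month 6, and that a fuller protocol may provide for this. That is fair, and it keeps the point modest. It does not remove it, because the article does not merely omit the timing. It states a schedule and sampling criteria, and neither provides for early discontinuation.

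**Conclusion.** The point holds as a limited weakness in data collection for a primary outcome. Structured post-exposure views of the diet are collected on a schedule that favours retained participants. About 12 of 60 people, at the plan's expected attrition, would have no set occasion to give them.

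A reader might conclude that this biases the decision to proceed. It does not. The protocol is judged viable without modification on recruitment, attrition and compliance alone, and none of these uses the questionnaire or the interviews. The consequence is confined to how the intervention and procedures would be modified for the definitive trial.

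The size of any distortion cannot be computed from the document. That the findings will lean towards favourable views rests on the assumption that leavers are, on average, less satisfied. That they will mainly describe stayers rests on following the stated schedule as written. This is a cheap improvement and not an error that invalidates the design.

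**What to change.** - **Process Evaluation:** schedule the questionnaire at baseline and at month 6, or at discontinuation if that comes earlier, by telephone or post at the contact where reasons for leaving are sought.
- **Interviews:** include consenting Diet2 discontinuers in the purposive sample, within the planned total of about ten.
- **Outcome measures:** report questionnaire results by arm alongside the number randomised, the number of non-responders and the reasons for discontinuation.

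An analysis that counts every silent leaver as finding the diet unacceptable need not be required, since some will have left for unrelated reasons.

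Cost: a wording change and about 0.20 × 60 = 12 short extra contacts at the expected attrition, with no additional interviews. Some leavers will not respond, and those lost to follow-up may be unreachable, so the gap narrows but does not close. Acceptability may also look less favourable than it would from stayers alone.

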#### Quality of life

One generic (EQ-5D) and one HIV-specific (MOS-HIV 35-item instrument) will be used to assess the impact of the trial on the participant's quality of life. These tools are deemed the most appropriate adjunct and HIV-targeted measures for use in HIV clinical trials.^66^ As responses to the EQ-5D thermometer tend to reflect physical more than mental health, the Warwick-Edinburgh Mental Well-being Scale (WEMWBS) will be used to measure mental well-being. The WEMWBS, a 14-item scale covering subjective well-being and psychological functioning, has been validated in the UK adult population.^67^ Permission has been granted to use these questionnaires in this study.

#### Interviews

Qualitative data will be collected from a sample of participants at the end of the 6-month intervention period. Participants will be purposively selected from the Diet2 arm to include men and women of different ethnicities, with high and low levels of adherence, to reflect the diversity and breadth of experiences of a wide range of participants. Semistructured interviews will be conducted using open-ended, non-directive questions. The aim will be to understand participants’ experience of implementing dietary changes by enabling them to ‘tell their story’—what they did and how—as well as identifying barriers to, and enablers of, success in making and maintaining diet changes. It is anticipated that there will be variations in the effectiveness of the dietary intervention for different individuals in different sociocultural settings. Analysis of the interview data will serve to describe and potentially explain these differences and the factors involved. By exploring participant views on the intervention, study design and delivery, the interviews will identify problems at the feasibility stage to prevent them occurring at the full trial stage.

Written informed consent for digital recording of the 30–60 min interview will be sought prior to booking a mutually agreed time and place, enabling the interview to be conducted either in participants’ homes or a clinic room with privacy. Participants will be encouraged to invite their partner, family member or other cohabitant to join in the interview and give their perspective on how dietary changes are lived.

The sample size will be around 10 although the actual number recruited will be determined at the point at which the researcher is satisfied that a good understanding of the barriers and facilitators to making dietary changes has been achieved.

Interviews will be transcribed verbatim. Data analysis will be conducted following the Framework Method: familiarisation, identifying a thematic framework, indexing, charting, mapping and interpretation.^68^
^69^ Data analysis and management will be supported by NVivo10 software (QSR International). A subset of interviews will be independently coded to verify interpretation. Where possible, data triangulation with cohabitants will be used to enhance plausibility, trustworthiness and transferability of the data analysis process. Reflective notes will be taken in a field note diary immediately after each interview and throughout data analysis, to maintain reflexivity of the researcher.

### Intervention design

All participants, in both groups, will be invited to attend three individual consultations with the research dietitian, and will receive further telephone reinforcement and support during the 6-month intervention period. Appointment times will be offered between 08:00 and 19:00, enabling flexibility for participants who are working. This will be followed by a 6-month maintenance period, with routine clinic visits only. The same research dietitian, experienced in HIV nutritional care, will provide all consultations.

#### Diet1: low saturated fat

Consultations will focus on reduction of saturated fat to <10% of energy intake, in line with UK guidelines^15^
^16^ and evidence on reducing the risk of CV events.^70^ Resources will be provided, such as written information, recipes and online videos, covering various topics including sources of saturated fat, food swaps, food labelling, cooking methods, cheese facts and margarine types.

On completion of the 12-month outcome measurements, participants in group 1 will receive the dietary information from Diet2 (Mediterranean Portfolio). Should they choose to adopt the diet, they will be given the option of having their fasting measurements repeated at month 18, at their routine blood test appointment.

#### Diet2: Mediterranean Portfolio

In addition to the information provided to group one, participants allocated to Diet2 will receive advice and support to adopt the Mediterranean Diet supplemented by additional functional foods with cholesterol-lowering properties. This will be embedded within a motivational interviewing style consultation to include assessing readiness to change, utilising decisional balance, reflective listening and open-ended questions, to identify needs, motivators and barriers to changing their diet, helping the participant to develop and verbalise arguments for change (desire, ability, reason need and commitment), and diminish resistance to it. The aim is to help empower and motivate the patient to make the changes identified during goal setting for their specific change plan. The dietitian will use the food diary to guide the participant towards the dietary changes most pertinent to their current intake while considering socioeconomic factors and family dynamics. The diet is not prescriptive, as goals will be negotiated individually with each participant during their first session and reviewed at each visit.

On the randomisation visit, daily consumption of 57 g tree nuts and 2 g plant stanols will be encouraged in the form of two handfuls of unsalted mixed nuts (almonds, cashew nuts, peanuts, Brazil nuts, hazelnuts, pecans, walnuts, pistachios, macadamia nuts) and a 50 mL cholesterol-lowering drink. At subsequent sessions, participants will be encouraged to continue with the nuts and stanols, while also aiming to eat 15 g/day soy protein as soya milk, yogurt or dessert, tofu and meat substitutes, and adopt a Mediterranean-style diet, with more vegetables and fruit, olive oil, and approximately 15–20 g/day soluble fibre from oats, pearl barley, lentils, beans and flaxseed. Supplies of the functional foods (nuts, soy protein, plant stanols, oats and pulses) will be given to participants to offset the additional cost of making dietary changes and inconvenience of searching for unusual items in supermarkets.

It is acknowledged that trials requiring longer term dietary change face challenges regarding attrition and adherence to study requirements, therefore some flexibility with dietary requirements will be provided in order to facilitate positive experiences and encourage commitment to the long term.^71^ If the participant is unable to consume the full amount of one component, for example, due to taste, they will be encouraged to maximise the contribution of other components.

In keeping with maintaining the integrity of a complex intervention, this trial will aim to standardise the function and process of the intervention, not the components themselves,^72^ thus allowing context-level adaptation, for example, use of ethnicity-appropriate resources. A sample of consultations will be audio recorded, for subsequent assessment by an HIV clinical psychologist, to monitor the quality of the motivational interviewing and fidelity of the intervention.

### Outcome measures

The primary outcomes for this study are feasibility and acceptability of trial procedures for recruitment, retention, data completion and the intervention. The protocol will be considered viable for a definitive RCT without modification if the following outcomes are met:
Recruitment rates of at least 50% of eligible patients;Attrition rate of <20% by 6 months;Compliance rate of 60% to trial.

If these outcomes are not met, the protocol will be modified in light of the study's findings.

Recruitment rate will be measured as proportion of eligible patients who are subsequently enrolled. Methods of recruitment will be compared: difference between recruitment rate from systematic methods (screening results) and ad hoc methods (posters, referral by multidisciplinary team). Reasons will be sought for declined participation. Appropriateness of eligibility criteria and their practical application for definitive trial will be explored.

Attrition rate is defined as both discontinuation and loss to follow-up of participants at 6 months. Logistic regression will be conducted to assess whether completion is associated with age, gender or allocation preference. Reasons for discontinuation will be sought from participants. The target of 20% (with precision of 10%) is based on the mean attrition rate from five Portfolio Diet studies (13%) and systematic review evidence (18%),^20^ although attrition has ranged from 25%^24^ to 42%^73^ in other HIV diet studies. Acceptability of the intervention and group allocation will be explored by questionnaire, and assessed by comparing attrition rates between the two groups.

Attendance to appointments, collection of supplied foods and completion of food diaries will be used as indicators of participation and study compliance.

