**Methods and analysis:**

60 adults with stable HIV infection on antiretroviral treatment and low-density lipoprotein cholesterol >3 mmol/L will be recruited from 3 West Midlands HIV services. Participants will be randomised 1:1 to 1 of 2 dietary interventions, with stratification by gender and smoking status. Participants allocated to Diet1 will receive advice to reduce saturated fat intake, and those to Diet2 on how to adopt the Mediterranean Portfolio Diet with additional cholesterol-lowering foods (nuts, stanols, soya, oats, pulses). Measurements of fasting blood lipids, body composition and arterial stiffness will be conducted at baseline, and month 6 and 12 of the intervention. Food intake will be assessed using the Mediterranean Diet Score, 3-day food diaries and metabolomic biomarkers. Questionnaires will be used to assess quality of life and process evaluation. Qualitative interviews will explore barriers and facilitators to making dietary changes, and participant views on the intervention. Qualitative data will be analysed using the Framework Method. Feasibility will be assessed in terms of trial recruitment, retention, compliance to study visits and the intervention. SD of outcomes will inform the power calculation of the definitive RCT.

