### Sample size

A CI approach was used to estimate the sample size required to establish feasibility.^48^ The criterion for success is that the definitive trial will be feasible if the attrition rate is <20% (or complete follow-up in at least 80% of all recruited participants). With a sample size of 60 participants, the expected attrition rate of 20% can be estimated with a 20% (95% CI 10% to 30%) margin of error. This upper bound of 30% is appropriate as it is the cut-off used to determine which trials constitute best evidence for behavioural intervention^49^ and which trials qualify to receive funding for implementation by the Centers for Disease Control and Prevention 2010.^50^

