Piloting this trial format will be important in determining any feasibility challenges and will be used to estimate the time, resources and sample size required for a full-scale RCT to answer these questions.

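### The go-criteria contain no number enrolled, so a pilot well short of 60 can still be declared viable without modification if attrition and compliance are met

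*Protocol article*

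**What the plan says.** The Outcome measures section of the protocol article gives the decision rule in full: "The protocol will be considered viable for a definitive RCT without modification if the following outcomes are met". The list that follows is "Recruitment rates of at least 50% of eligible patients;Attrition rate of <20% by 6 months;Compliance rate of 60% to trial". The same section then defines the first item: "Recruitment rate will be measured as proportion of eligible patients who are subsequently enrolled".

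The number 60 appears elsewhere. The abstract says that 60 adults "will be recruited from 3 West Midlands HIV services", and the Sample size section justifies that number by precision: "With a sample size of 60 participants, the expected attrition rate of 20% can be estimated with a 20% (95% CI 10% to 30%) margin". It defends the upper limit of 30% as a cut-off used to judge behavioural trials. Neither place links the number 60 to the go decision.

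The Statistical analysis plan section reports the number recruited descriptively and sets no threshold for it. The Discussion says that the pilot "will be used to estimate the time, resources and sample size required for a full-scale RCT".

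**The concern.** A recruitment proportion with eligible patients as its denominator measures willingness to join. It does not measure whether the three services can supply enough patients, or how quickly. The other two conditions are also percentages, so missing the planned sample cannot by itself change the verdict.

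Two things are at stake. First, recruitment feasibility is among the primary outcomes, and the pilot is meant to inform the time needed for the full trial. The formal verdict could nevertheless certify, as needing no change, a design that did not recruit its own target. Second, the attrition condition compares an observed percentage with 20% and takes no account of its uncertainty. Its reliability rests on the sample size, and the sample size is outside the rule.

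**Working it through.** **Inputs.** Planned n = 60, expected attrition 20%, stated 95% CI 10% to 30%, and 30% as the upper bound that matters (Sample size). Conditions of at least 50% uptake, attrition below 20%, and 60% compliance (Outcome measures). The smaller sample sizes below are assumptions, chosen to show a range.

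**1. The plan's own figure.** Wald interval, p ± 1.96 × √(p(1−p)/n):

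0.20 ± 1.96 × √(0.20 × 0.80 / 60) = 0.20 ± 0.101, i.e. 9.9% to 30.1%.

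This reproduces the stated 10% to 30%.

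**2. The recruitment condition does not depend on scale.** 60/120 = 30/60 = 10/20 = 50%. All three meet it, over any duration.

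**3. Precision if enrolment falls short** (same formula, attrition 20%):

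| n | half-width (points) | 95% CI |
|---|---|---|
| 60 | 10.1 | 9.9% to 30.1% |
| 50 | 11.1 | 8.9% to 31.1% |
| 40 | 12.4 | 7.6% to 32.4% |
| 30 | 14.3 | 5.7% to 34.3% |
| 20 | 17.5 | 2.5% to 37.5% |

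These intervals show the loss of precision only. An observed 20% does not meet a condition of less than 20%, so they do not describe a pilot that passes.

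**4. The least favourable result that still passes.** The largest count strictly below 20% is 11, 7, 5 and 3 at n = 60, 40, 30 and 20. Wald upper limits:

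- 11/60: 0.183 + 1.96 × √(0.183 × 0.817 / 60) = 28.1%
- 7/40: 0.175 + 1.96 × √(0.175 × 0.825 / 40) = 29.3%
- 5/30: 0.167 + 1.96 × √(0.167 × 0.833 / 30) = 30.0%
- 3/20: 0.150 + 1.96 × √(0.150 × 0.850 / 20) = 30.6%

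Exact (Clopper-Pearson) upper limits are higher: 30.4% at 11/60, 34.7% at 5/30 and 37.9% at 3/20.

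**5. Chance of meeting the attrition condition.** Exact binomial P(X ≤ c), with c as in step 4:

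| true attrition | n=60 | n=40 | n=30 | n=20 |
|---|---|---|---|---|
| 15% | 81.9% | 75.6% | 71.1% | 64.8% |
| 25% | 14.8% | 18.2% | 20.3% | 22.5% |
| 30% | 2.9% | 5.5% | 7.7% | 10.7% |

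A smaller pilot discriminates less in both directions: poor retention passes more often and good retention passes less often. True rates of 25% and 30% are not far-fetched, since the Outcome measures section itself cites 25% to 42% in other HIV diet studies.

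**The case against.** The strongest reply is that nothing stated is wrong. The plan commits to 60, its precision at 60 is correct, and any trial loses precision if it under-recruits. Uptake among eligible patients is a legitimate feasibility measure. The number recruited will be reported, binary outcomes get a 95% CI (necessarily at the achieved n), the suitability of the eligibility criteria will be explored, and a Trial Steering Committee supervises. A shortfall would therefore be visible. This stands as far as reporting goes, but none of it enters the rule that produces the verdict.

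Three stronger readings are tempting, and the document does not support them.

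- A reader might infer that a stalled pilot passes on recruitment alone. It does not: attrition and compliance must also be met.
- A reader might take the intervals in step 3 to show that a passing pilot far exceeds the 30% bound. For results that actually pass, the Wald upper limit only reaches 30% at about n = 30 among the sizes shown, and the rise in false passes is modest.
- A reader might infer that too few eligible patients is a likelier failure than refusal, because the entry criteria are narrow. The article gives no clinic size, prevalence or refusal rate, so this cannot be judged.

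The article also condenses a fuller protocol, and a recruitment period may be stated there. Its absence here is not the point. The point is that the stated list of conditions, as defined, has no element of number or time.

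**Conclusion.** The point holds in a limited form. The recruitment condition is met whatever the number enrolled. When the attrition and compliance conditions are also met, a pilot well short of 60 is declared viable without modification. The precision given for n = 60 is correct as planned.

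The statistical consequence is moderate and depends on a shortfall. At true attrition of 30%, halving enrolment to 30 raises the chance of meeting the attrition condition from 2.9% to 7.7%, and at n = 20 it is 10.7%. The Wald upper limit for the worst passing result rises from 28.1% to 30.0% and 30.6%. At n = 50 the loss is small (half-width 11.1 instead of 10.1 points). These figures assume independent dropout with a common probability.

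The larger consequence is one of logic rather than precision: the formal verdict can overlook a failure to reach the pilot's own target. This is a worthwhile, inexpensive improvement to the decision rule and does not invalidate the trial.

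**What to change.** Keep the 50% uptake condition. Add a fourth condition to the list in Outcome measures: the planned 60 participants are enrolled within the sponsor's planned recruitment period (the article does not state this period, so the sponsor must supply it). Report accrual per site per month, which also serves the aim of estimating the time needed for the full trial.

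State that if fewer than 60 are enrolled, the protocol is not declared viable without modification. In that case attrition is read with its 95% CI at the achieved n against the 30% bound of the Sample size section. Name the interval method in advance, because the exact upper limit is already 30.4% at 11/60 while the Wald limit is 28.1%.

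**Cost.** One added condition, with no extra visits or measurements. Enrolment dates by site must be recorded; the article does not say whether they are. The favourable verdict will be reached somewhat less often, including in a pilot that misses 60 by only a few and loses little precision.
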